## Abstract

**Background:**

After regular treatment, patients with persistent depressive disorder (PDD) may remain in specialized psychiatric outpatient care without achieving remission. Lacking other options, these patients often receive long-term, non-protocolized care as usual (CAU) that does not involve the partner/caregiver of the patient. Although the revised depression treatment guidelines suggest focusing on psychiatric rehabilitation and self-management as the next treatment step for PDD, an evidence-based cost-effective self-management protocol for PDD is lacking. This study investigates the “Patient and Partner Education Program for All Chronic Illnesses” (PPEP4All) as a brief self-management protocol that could lead to lower costs, higher quality of life, and less disease burden in PDD patients and their partners/caregivers.

**Methods:**

Presented is the rationale and methods of a multicenter pragmatic randomized controlled trial to evaluate the clinical efficacy and cost-effectiveness of PPEP4All for patients with PDD and their partners/caregivers. In accordance with current recommendations, a mixed methods research approach is used with both quantitative and qualitative data. A total of 178 eligible outpatients with PDD and their partners/caregivers are recruited and randomized to either PPEP4All or CAU. Those assigned to PPEP4All receive nine weekly self-management sessions with a trained PPEP4All therapist. Primary and secondary outcome measurements are at 0, 3, 6, and 12 months.

**Discussion:**

This project will result in the implementation of a self-management intervention for patients with PDD, meeting an urgent need in mental healthcare. Using PPEP4All can optimize the quality and efficiency of care for both patients with PDD and their partners/caregivers.

**Trial registration:**

Netherlands Trial Register Identifier NTR5973. Registered on 20 July 2016.

**Supplementary Information:**

The online version contains supplementary material available at 10.1186/s13063-021-05666-y.

## Background

Approximately 10–17% of persons with major depressive disorder (MDD) suffer a chronic course, or a continuous period of at least 2 years [1]. Two types of depressive disorders have a prolonged duration: chronic major depressive disorder and dysthymic disorder [2]. These were combined into one syndrome, persistent depressive disorder (PDD), in the latest Diagnostic and Statistical Manual of Mental Disorders (DSM-5) [3]. Compared to less persistent forms of depression, PDD has a 3–6% lifetime prevalence [3–7] and adverse consequences for patients, such as impaired functioning in social and family relationships, high disease burden for both patient and partner/caregiver, reduced performance in work, comorbid psychiatric and somatic problems, and an increased suicide risk [8, 9].

Many patients with PDD remain in specialized outpatient care without achieving remission, even after having been treated according to the international multidisciplinary depression guidelines [4, 10–12]. Clinicians are resigned to providing long-term supportive non-specific treatment (i.e., care as usual), due to the considerable suffering of patients and the absence of alternative treatment options [13]. More intensive prolonged care, however, often fails to improve therapeutic response; previous research has shown that patients with increasing depression symptom levels have a poor treatment prognosis despite receiving more intensive care [14–16]. The ongoing unsuccessful treatment leaves both patients and clinicians feeling powerless and frustrated [13]. Moreover, this treatment often disregards the partner/caregiver of the patient, although involvement of the partner/caregiver has been shown to be beneficial in improving treatment results of the patient and reducing the partner’s psychosocial burden concerning patient’s disease [17–21].

The revised multidisciplinary guidelines for depression treatment [11, 22–27] advise focusing on psychiatric rehabilitation as the next therapeutic step for PDD patients with inadequate treatment results. Psychiatric rehabilitation using self-management interventions focuses less on symptom recovery and more on restoring psychosocial functioning and enhancing patient autonomy. Individuals with PDD learn to set realistic goals (e.g., regarding work reintegration) and to cope by adjusting their activities to compensate for restrictions caused by the chronic illness. To date, there is still an urgent need in specialized mental healthcare for a brief evidence-based, cost-effective treatment protocol concerning self-management for treatment-resisting persons with PDD that also involves the partner/caregiver and replaces long-term non-specific usual care.

As a possible solution, we propose the use of the self-management program named the “*Patient and Partner Education Program for All Chronic Illnesses*” (PPEP4All). This program was originally named the “*Patient and Partner Education Program*” (PPEP) and developed for homogenous groups of patients with chronic somatic diseases, like Parkinson’s disease and Huntington’s disease, and tested by EduPark, a research consortium with seven participating European countries [18, 28–30]. Later, PPEP was tested in a heterogeneous group of patients with various chronic somatic disorders and comorbid long-term depression and/or anxiety, with positive results, after which the program name was changed to PPEP4All [18]. The structure and substance of the eight sessions are the same; however, the wording of the program and workbooks was altered for inclusivity of various diseases [31–33], and the present PPEP4All program includes one additional session regarding coping with chronic depression (i.e., “Suicide prevention & relapse plan”).

Research has already shown that PPEP is effective: patients with Parkinson’s disease showed a significant improvement in quality of life after completion of PPEP [19]. Moreover, patients with symptom-present Huntington’s disease showed a significant improvement in active coping and seeking social support and reported fewer behavioral problems and less anxiety. After 6 months, they also showed an improvement in psychosocial burden related to their chronic illness [34]. Patients with chronic pituitary disorders showed significant higher self-efficacy after following PPEP [35]. Moreover, after following PPEP4All, patients with various chronic somatic disorders and comorbid chronic depression showed an improvement in depression scores [18]; an indication that PPEP4All could also be applied to mental healthcare, which was the starting point for the present study. The cost-effectiveness of PPEP/PPEP4All has not yet been investigated.

The present study evaluates the clinical- and cost-effectiveness of PPEP4All in patients with PDD and their partners/caregivers. Additionally, this project aims to further our understanding of the healthcare needs for patients with PDD and elicit direct feedback about PPEP4All from patients, partners/caregivers, and clinicians via qualitative interviews. Compared to usual care for PDD, we expect that PPEP4All will lead to an improved quality of life, fewer psychiatric symptoms, and more mental resilience in patients (using superiority testing). Second, we expect that PPEP4All will lead to lower psychosocial burden from chronic depression for both patients and their partner/caregiver. Third, due to the briefness and anticipated higher effectiveness of PPEP4All, we expect lower societal and healthcare costs, compared to care as usual.

## Methods

### Study design

In this multicenter, pragmatic randomized controlled trial (RCT), the protocolized PPEP4All self-management intervention is evaluated against care as usual (CAU) in specialized outpatient mental health care clinics in the Netherlands. Measurements are at 0 (pre-treatment), 3 (post-treatment), 6 (first follow-up), and 12 months (second follow-up), with assessors/data-analysts blind to randomization status. In accordance with current recommendations (in the context of RCTs) [36–41], we use a mixed methods research approach with both quantitative and qualitative data, where the qualitative study is nested in the main RCT project. The qualitative data complements the quantitative data and can facilitate the practical implementation of the intervention, strengthen the clinical relevance of our results, and optimize the PPEP4All intervention by adding the perspectives of patients, partners/caregivers, and clinicians. Moreover, the study protocol conforms to the Standard Protocol Items: Recommendations for Interventional Trials (SPIRIT) guidelines (see Additional file 1).

### Setting and participants

Eligible patients are recruited from five Dutch mental healthcare organizations, with 11 individual locations, that offer outpatient treatment for depressive disorders (see Acknowledgements). The primary/lead research center of the study is the Department of Psychiatry of the Leiden University Medical Center (LUMC). The inclusion criteria for participating patients are as follows: (1) diagnosis of recurrent or chronic major depressive disorder (duration of at least 2 years) according to the DSM-IV [2] or PDD according to the DSM-5 (non-severe comorbidity is allowed, e.g., anxiety disorder) [3]; (2) age of 18 years or older; (3) treatment indication for rehabilitation as specified by the clinician, with a minimum of at least one previous psychological treatment and at least two medication trials, with unsatisfactory results, according to the international multidisciplinary guidelines for depressive disorders [11, 22–27]. Patients with recurrent or chronic depression who do not wish to complete all treatment steps of the depression guideline (e.g., refuse medication) can also enroll in the study. Patients with bipolar disorder type II may also participate considering they generally spend much more time in a depressed state than in a hypomanic state, making it difficult to differentiate from recurrent depression [42]. Exclusion criteria for patients are as follows: severe psychopathology (e.g., schizophrenia, current psychotic state, severe substance addiction, bipolar disorder type I); acute and severe risk of suicide; severe somatic disorders that are too disabling or render the patient immobile; severe cognitive problems such as dementia; expected dosage adjustments of medication during PPEP4All; and insufficient fluency in the Dutch language.

The inclusion criteria for partner/caregiver to participate in the study and PPEP4All program for partners/caregivers are as follows: (1) ability to participate in at least three sessions of the intervention, (2) not currently receiving active psychotherapy, and (3) agreement from the patient for the partner/caregiver to participate.

### Recruitment, enrollment, and allocation

Psychiatric nurses and psychiatrists of the participating mental healthcare locations identify patients eligible for participation according to the above inclusion/exclusion criteria, and they introduce research participation and provide information letters. Patients who are interested and consent to participate in the study sign an informed consent form, which is then sent to the primary research center (LUMC). On this informed consent form, participants also indicate whether they want to be invited to a follow-up nested qualitative interview study in which we evaluate their satisfaction with PPEP4All and their process of implementing coping strategies for chronic depression (see section “Qualitative data”).

To check the inclusion and exclusion criteria formally, a trained research assistant checks the DSM-IV depressive disorders with the Dutch translation of the Mini-International Neuropsychiatric Interview (MINI interview, modules A, B, and C regarding depression, dysthymia, and suicidality). The MINI interview is a well-validated diagnostic interview used to identify psychiatric disorders, with excellent interrater and test-retest reliability [43, 44].

Allocation of participants is performed by an independent data coordinator/data manager, who is not involved in the data collection/analysis (GC; see Acknowledgements). Participants are allocated to either PPEP4All or CAU, using a stratified randomization schedule (stratified by gender and research center) designed by an independent statistician of the Department of Medical Statistics and Bioinformatics of the LUMC.

For the patients allocated to PPEP4All, their main caregiver (e.g., partner, close family member, or close friend) is invited to participate in the project. The data manager makes an appointment with the partner/caregiver, and they sign an informed consent before the first measurement. All participants are informed that participation is voluntary and that they can withdraw from the study at any time without consequences. Participants receive a 20-euro gift card to thank them for their efforts. An overview of the study design and patient flow is provided in Fig. 1.

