## Sample size and power calculation

We based our sample size on the effect size of previously conducted randomized controlled trials that evaluated relevant interventions in a similar setting in patients with chronic or treatment-resistant depression and that reported a quality of life outcome measure [83, 84, 88–90]. We can expect an effect size around 0.35 [90]. Considering a power level of 80%, alpha of 95%, and equal allocation ratio, we would require 81 participants per group [91–95]. With an additional 16 persons to account for an expected attrition of 10% [96], we expect to include a total sample of 178 participants (2 × 89).

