### Clinical effectiveness

The mean quality-adjusted life years (QALYs) are estimated using EQ-5D-5L data from four assessments. For the *primary data analysis*, we perform an analysis of covariance for the QALY’s using the post-test EQ-5D-5L results with the pre-test scores as covariate [92–94]. In this way, we test whether there is a difference between PPEP4All and CAU, accounting for the variation where the patients started at the first measurement. For the *secondary data analyses*, secondary parameters are tested using weighted generalized estimating equation (GEE) analyses [97, 98]. Clinical effectiveness analyses are examined using superiority testing.

Moreover, we examine tailored care by further investigating for which groups PPEP4All is the most effective. If possible, subgroup analyses are performed for age, gender, ethnicity, and intervention modality (group/individual). In this context, we explore relevant socio-demographics (e.g., education, living situation, and work) and clinical variables (e.g., comorbidity, baseline severity of disease).

For all outcome analyses, an intention-to-treat (ITT) approach is used, according to the CONSORT statement [99]. Analyses are conducted in SPSS, Stata or R.

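### Allocation is stratified by gender and research center, but the primary ANCOVA as stated names only the pre-test score; if those factors predict outcome, its reported standard error is too large and the test conservative.

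*Protocol article*

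**What the plan says.** Under Recruitment, enrollment, and allocation, the protocol article says that participants are allocated "using a stratified randomization schedule (stratified by gender and research center"). Under Setting and participants, patients are "recruited from five Dutch mental healthcare organizations, with 11 individual locations". The article does not say which of these two units is the research center used as a stratum.

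Under Clinical effectiveness, the primary analysis is an analysis of covariance for the QALYs "using the post-test EQ-5D-5L results with the pre-test scores as covariate". The stated purpose is to account for where patients started. No other covariate is named. Gender returns in that section only as a subgroup variable, and center does not appear in the quantitative analysis text. Secondary outcomes are to be tested with weighted GEE, for which no covariates are named.

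**The concern.** Stratified allocation forces the arms to be similar on gender and center, so differences between strata contribute little to chance variation in the treatment contrast. An ordinary ANCOVA without those factors does not know this. It leaves the between-stratum variance in its residual and builds the standard error from it. Whenever the factors predict outcome beyond the baseline score, the reported standard error exceeds the true one.

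The stake is modest but real: intervals wider than the data warrant, a test run below its nominal 5%, and some power given away. A center effect is plausible on the article's own description. Several organizations deliver usual care that follows no protocol, and PPEP4All is given by 34 therapists in groups or individually.

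**Working it through.** **Inputs from the protocol article**
- Stratification factors: gender and research center. With five organizations or 11 locations this gives 5 × 2 = 10 or 11 × 2 = 22 strata.
- Primary model: ANCOVA with the pre-test score as the only named covariate.
- Sample size: effect size 0.35, 80% power, 81 per group, so 162 analyzed; 178 with attrition.

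**Assumptions not in the article**
- R², the share of outcome variance left after baseline that gender and center explain: 2%, 5% or 10%.
- Two-sided 5% test.
- Strata balanced almost perfectly between the arms.

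**The plan's own figure.** The 81 per group does not follow from the stated inputs for a plain two-group comparison, which needs 129 per group two-sided or 101 one-sided. It is reached two-sided if the pre/post correlation is about 0.61, because 128.1 × (1 − 0.607²) ≈ 81. That is a separate matter. Here 162 patients and a nominal 80% power serve only as the reference point, so the standardized effect under the alternative is 1.96 + 0.84 = 2.80.

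**Formulas.** Let s = √(1 − R²). Under balanced strata, the true standard error is s times the one the pre-test-only model reports.
1. Interval width, reported over correct: 1/s.
2. True type I error of the pre-test-only model: 2 × [1 − Φ(1.96/s)].
3. Power of the pre-test-only model: Φ((2.80 − 1.96)/s).
4. Power of the model with gender and center: Φ(2.80/s − 1.96).
5. Extra patients the pre-test-only model needs to match (4): 162 × {[(2.80 + 1.96 × (1 − s))/2.80]² − 1}.

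| R² | s | Interval too wide by | Type I error | Power, pre-test only | Power, adjusted | Gain (points) | Extra patients |
|---|---|---|---|---|---|---|---|
| 2% | 0.990 | 1.0% | 4.8% | 80.2% | 80.8% | 0.5 | 2 |
| 5% | 0.975 | 2.6% | 4.4% | 80.6% | 82.0% | 1.4 | 6 |
| 10% | 0.949 | 5.4% | 3.9% | 81.2% | 84.0% | 2.7 | 12 |

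Gains are taken before rounding. At 10%, for example: 1.96/0.949 = 2.066, so type I error is 3.9%. The two powers are Φ(0.887) = 81.2% and Φ(0.993) = 84.0%. The patient equivalent is 162 × [(2.902/2.802)² − 1] ≈ 12.

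**Check by simulation.** 4,000 runs per setting; 162 patients; 5 or 11 equal centers; permuted blocks of 4; a 60/40 gender split; pre/post correlation 0.61. The design details are assumptions.
- R² = 0: both models reject at about 5% under the null. With 11 centers, power is 79.2% without the strata and 78.5% with them.
- R² = 5%: null rejection is 4.4–5.0% for the pre-test-only model. Power is 79–80% against 80%.
- R² = 10%: the pre-test-only model reports a standard error of about 0.125 against an actual 0.117–0.120. Null rejection is 3.5–4.2%. Power is 81% against 84%.
- R² = 20%: null rejection is about 3.1%. Power is 82–83% against 87–88%.
- Across all settings the adjusted model rejects at 4.5–5.6% under the null.

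The actual spread of the estimate is nearly the same under both models: at 10%, 0.117–0.120 without the strata and 0.116–0.120 with them. The difference lies in the reported standard error.

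**The case against.** The strongest reply is about scope. This is a condensed article and no statistical analysis plan is shown. The sentence on the primary analysis names one covariate; it does not say that it is the only one, nor that the stratification factors are left out. A full plan may list them. That stands as a limit: a reader might infer that the trial has decided against adjusting for gender and center, and the article does not support that. But the article does state a primary model, and that model does not reflect the stratified allocation described in the same paper.

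The second reply is that the harm is conditional and small. This stands too. The article gives no figure for how far gender or center predicts outcome. With nothing to explain there is no loss, and any error is in the safe direction. With 10 or 22 strata for 178 patients, about 18 or 8 per stratum, incomplete blocks would leave some imbalance and shrink the conservatism. The block scheme is not given.

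Three stronger readings are tempting. One is that false positives are inflated or the estimate biased; the calculation shows a test at or below 5%, and the allocation is random. Another is that the stated model throws away precision; the estimate is almost as precise either way, because the design has already balanced the factors. The third is that adjusting gains 0.8, 2.0 or 4.0 points, worth about 3, 9 or 18 patients. That compares the adjusted model with a flat 80%, whereas stratified allocation already lifts the pre-test-only test slightly above it.

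Doubts about the 81 per group are a separate issue and add no weight here.

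**Conclusion.** The point holds in conditional form. The primary model as stated does not carry the factors used to randomize. If gender or center predicts outcome beyond baseline, the cost is a slightly conservative test and an interval 1% to 5.4% too wide over R² of 2% to 10%, with at most about 2.7 points of power at stake in that range. These sizes rest on an assumed R², near-perfect balance and a two-sided 5% test at a nominal 80% power. This is a minor defect in the safe direction, worth correcting because the remedy is nearly free and settles the covariates before the data are analyzed.

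**What to change.** Add one sentence to the analysis section: gender and research center enter the primary ANCOVA alongside the pre-test score, and enter the secondary GEE models, with center defined at the level used in the randomization schedule (organization or location). If the full analysis plan already says this, the article need only say so.

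The cost is 1 degree of freedom for gender plus 4 for five organizations or 10 for 11 locations, so 5 to 11 out of about 160. If the factors turn out not to be prognostic, the price is a trace of power: in the simulation with 11 centers, 79.2% against 78.5%.

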**Fig. 2 Fig2:**
[figure not shown]
Standard Protocol Items: Recommendations for Interventional Trials (SPIRIT) schedule of enrollment, interventions, and assessment of the study. Notes: MINI = Mini-International Neuropsychiatric Interview [35, 36]. EQ-5D-5L = EuroQoL-5 with visual analogue scale [40–44]. TiC-P = Trimbos Medical Technology Assessment questionnaire for psychiatric illness-associated costs [45]. IDS-SR = Inventory of Depressive Symptomatology, self-rated [46–48]. SQ-48 = Symptom Questionnaire-48 [49–52]. SRH = self-rated happiness [53–55]. BRSnl = Brief Resilience Scale [56, 57]. B4CZ = Questionnaire on Burden of Chronic Disease for Patients (or Partners) [58, 59]. ^a^The PPEP4All intervention is mainly provided as a group treatment but can also be offered as an individual treatment. ^b^These questionnaires are administered to partners/caregivers in the study

At the first measurement (i.e., 0 months), participant demographics are registered, and the primary and secondary outcome questionnaires are completed. At the second, third, and fourth measurements (i.e., 3, 6, and 12 months), the outcome questionnaires are again completed.

The *primary outcome measures* pertain to quality of life and healthcare costs (see Fig. 2). Quality of life is measured for both patients and partners/caregivers using the EuroQoL-5 (EQ-5D-5L, including the visual analogue scale, 5 items) [48–52]. Using the EQ-5D-5L, we calculate the mean quality-adjusted life years (QALYs) gained, which is used in the cost-effectiveness analysis (CEA; see “Economic evaluation”). Healthcare consumption (such as contact with healthcare professionals, medical costs, and productivity loss) are measured with the Trimbos Medical Technology Assessment questionnaire for psychiatric illness-associated costs (TiC-P; 30 items) [53].

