### Care as usual (CAU)

To compare PPEP4All with what is currently being offered in mental health clinics, the participants randomized to the control group receive care as usual (CAU), thus increasing the ecological validity of the present study. This standard treatment for patients with PDD concerns mostly long-term, non-protocolized supportive care from a psychiatric nurse, with pharmacological maintenance therapy from a psychiatrist. CAU mostly has an individual treatment modality and does not include the partner/caregiver of the patient. Patients allocated to CAU in this study generally continue the standard treatment with their own therapist.

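### As written, caregivers enter only from the PPEP4All arm, so their outcomes have no concurrent control and cannot support a comparison with usual care; the patient comparison is unaffected

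*Protocol article*

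**What the plan says.** On who enters, Recruitment, enrollment, and allocation first describes allocation and then says: "For the patients allocated to PPEP4All, their main caregiver (e.g., partner, close family member, or close friend) is invited to participate in the project". Caregiver consent and the caregiver's first measurement follow that invitation. Setting and participants gives a single set of caregiver criteria, covering both the study and the program. The first is "ability to participate in at least three sessions of the intervention". Under Care as usual (CAU): "CAU mostly has an individual treatment modality and does not include the partner/caregiver of the patient". The two interview parts (Coping with chronic depression; Satisfaction) name caregivers from PPEP4All only, although patients may come from either arm.

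On what is expected of caregivers, the first numbered expectation in Background opens with "Compared to usual care for PDD, we expect that PPEP4All will lead to an improved quality of life" and concerns patients. The second reads: "Second, we expect that PPEP4All will lead to lower psychosocial burden from chronic depression for both patients and their partner/caregiver". Assessment and instruments says, under the primary outcome measures: "Quality of life is measured for both patients and partners/caregivers using the EuroQoL-5". The partner version of the burden questionnaire (B4CZ partners) is a secondary outcome. Clinical effectiveness tests secondary parameters by weighted GEE and applies superiority testing to the clinical effectiveness analyses, with no exception for caregivers.

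The abstract's Methods paragraph says: "A total of 178 eligible outpatients with PDD and their partners/caregivers are recruited and randomized to either PPEP4All or CAU".

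**The concern.** The enrolment route and the claims do not match. The route supplies caregivers from one arm, after the allocation is known. The claims speak of lower caregiver burden, list a caregiver measure under a primary outcome, and can be read in the abstract as randomization of patient-caregiver pairs.

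The caregiver conclusion is what is at stake. Involving the caregiver is the first advantage that the article claims over other self-management programs, so caregiver results will attract attention. A reader of the abstract would take them as randomized evidence. They would in fact be changes over time in people who accepted an invitation knowing the arm and who could attend sessions. Regression to the mean, time trends and expectation could produce such a change without any effect of the program.

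**Working it through.** **1. The plan's own figures.** Sample size and power calculation gives 81 per group plus 16 for attrition: 2 × 81 + 16 = 178, or 2 × 89. The abstract applies the 178 to outpatients, and the effect size comes from trials in patients. No caregiver number is given. With one main caregiver per PPEP4All patient, the caregiver sample is at most 89; uptake is not stated. For CAU no entry route is described, so the count as the text reads is 0.

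**2. The passages side by side.**
- Invitation: PPEP4All patients' caregivers only.
- Eligibility: attendance at intervention sessions, which a CAU caregiver does not have.
- Comparator treatment: excludes the caregiver.
- Caregiver interviews: PPEP4All only.
- Abstract: names both arms but gives no procedure for recruiting or measuring a CAU caregiver.

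The first four agree with one another. Only the abstract points the other way.

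**3. Can an arm effect be estimated?** The contrast is Δ = μ(PPEP4All) − μ(CAU), with variance σ²(1/n₁ + 1/n₀). With n₀ = 0 there is no estimate of μ(CAU), and the variance is undefined. A GEE does not help. The arm indicator equals 1 for every caregiver, so it coincides with the intercept, and an arm-by-time term coincides with time. Only the time effect within PPEP4All is estimable.

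**4. What the time effect contains.** Observed mean change = program effect + change that would have occurred anyway (trend, regression to the mean) + expectation. One observed quantity cannot separate these components.

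**5. Which analyses are touched.**
- Primary analysis of covariance (Clinical effectiveness): adjusts for where patients started. Not touched.
- QALYs (Economic evaluation): computed per patient. Not touched.
- Costs (Cost-effectiveness analysis): compared per patient. The caregiver time counted there is time at PPEP4All meetings, which do not exist under CAU. Not touched.
- Caregiver EQ-5D-5L and B4CZ partners: no control. Touched.

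**6. Could CAU caregivers still be added?** Trial status gives recruitment from 1 April 2017 to 1 April 2021 (48 months) and a protocol version dated 1 February 2021, leaving 2 months. At an even rate (assumed), 178 × 2/48 = 7.4 patients remain, about 3.7 of them in CAU. At three times that rate (assumed), 22.3 remain, about 11.1 in CAU. These are upper limits for CAU caregivers at one per patient, and nearly all would be measured later than most PPEP4All caregivers.

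**The case against.** The strongest reply concerns scope. No described analysis uses caregiver EQ-5D-5L as a primary endpoint, and the listing in Assessment and instruments may be loose wording. This stands. A reader might infer that part of the primary analysis is lost, but the documents do not support that: step 5 shows the primary comparison to be in patients and intact.

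Second, the comparator phrase and the mention of superiority testing in Background sit in the first expectation, which is about patients. The second expectation repeats neither. This is partly right: the comparison for caregivers is inferred. It is still the natural reading. The word for lower burden needs a comparator, the third expectation again names care as usual, and Clinical effectiveness applies superiority testing without exempting caregivers.

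Third, the abstract sentence may be mere compression, with patients randomized and caregivers accompanying them. That is possible, and a reader should not conclude that caregivers were in fact to be randomized. Even so, the sentence suggests caregivers in both arms and needs aligning with the methods.

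Fourth, a reader might take it as established that no CAU caregiver is ever measured. The article does not say so outright. The flow diagram and the assessment schedule are not shown, and the visible schedule note speaks of caregivers in the study without naming an arm. The absence is a strong inference from four consistent sections. If CAU caregivers are in fact enrolled, the eligibility and recruitment text is wrong, so a correction is due either way.

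Finally, collecting caregiver data only from program users is a reasonable pragmatic choice. That supports describing them, not comparing them with usual care.

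**Conclusion.** The concern holds for caregiver outcomes only. As written, the design gives at most 89 PPEP4All caregivers and no CAU caregivers. It therefore cannot support the expectation of lower caregiver burden than under usual care, or superiority testing of caregiver EQ-5D-5L or B4CZ partners. This is not a detail that an analysis plan could settle, because the control data would not exist.

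The randomized evidence on patients stands in full. The conclusion assumes that the unshown figures contain no CAU caregiver assessments; the maximum of 89 assumes one caregiver per patient.

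**What to change.** Four changes to the text:

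- **Abstract, Methods:** reconcile with Setting and participants and with Recruitment, enrollment, and allocation, so that only patients are described as randomized.
- **Assessment and instruments:** state that the primary quality-of-life outcome is the patients' EQ-5D-5L.
- **Background and Clinical effectiveness:** take caregivers out of the comparative hypothesis and out of superiority testing.
- **Caregiver EQ-5D-5L and B4CZ partners:** label the results as uncontrolled, within-arm before-after descriptions in self-selected caregivers, here and in later reports.

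These cost only an edit and carry through to the trial report. No new data are needed.

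Starting to enrol CAU caregivers is not recommended. It would need new caregiver eligibility criteria, caregiver consent, ethics review and assessments at 0, 3, 6 and 12 months. With about two months of planned recruitment left, it would yield a handful of largely non-concurrent controls (step 6 of the working), which is not a usable comparison group.
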